### Hospital anxiety and depression scale

We will also use the HADS as a secondary check of depression and anxiety as it is widely used in similar research projects [32]. The HADS is a 14-item questionnaire with seven of these items assessing level of anxiety and seven assessing depressive symptoms. Each item is rated on a scale from 0 to 3; therefore, there is a maximum score of 21 for anxiety and 21 for depression. The higher the score, the more severe are the anxious or depressive symptoms. The HADS was found to be a reliable measure of anxiety and depression in a large study of out-patients. Furthermore, the subscales are valid, with higher scores indicating greater severity of the disorder [32].

### Work and social adjustment scale

The WSAS will be used to assess levels of social functioning [34]. The WSAS is a five-point questionnaire addressing life activities. The questionnaire probes issues relating to the impact the disorder in question is having on the individual’s everyday life and functioning. Responses are given on a scale of 0 to 8, with higher scores indicating higher level of impairment or disruption to social functioning. Therefore, the maximum score on this questionnaire is 40. Mundt and colleagues [34] state that, in light of studies that included two clinical groups, in those with depression and those with obsessive-compulsive disorder, a score below 10 on the WSAS does not indicate clinically significant problems and between 10 and 20 indicates significant impairment. Those scoring over 20 are likely to have significant problems in their social functioning [34]. The WSAS has strong psychometric properties, showing good reliability and validity in patients with depression and in a sample of patients with obsessive-compulsive disorder, with greater severity of symptoms being strongly associated with functional impairment [34].

### The client satisfaction questionnaire

The client satisfaction questionnaire (CSQ-8) will be administered post-intervention as a measure of satisfaction with the intervention. The CSQ-8 is an eight-item questionnaire rated using a four-point Likert scale. Scores range from 8 to 32 with higher scores indicating greater satisfaction with the intervention in question. A series of studies of this measure have indicated high internal consistency (Cronbach’s alpha 0.92 to 0.93 for eight-item scale) as well as criterion and construct validity [35].

### Follow-up

Participants will be offered a £10 Amazon/Tesco voucher in return for completed follow-up questionnaires. This is expected to improve follow-up rates and help us to achieve our target of getting at least a 70% response rate. Additionally, in order to maintain contact with participants during the delay before follow-up assessments are posted out, greetings cards or letters will be sent. In these, the IA participants will be given details of their final Planning for the Future/Revision class and next assessment point. The DAC participants will be thanked for their patience, given details of the next evaluation assessment and will be given an approximate start date for their course.

#### Statistical power and sample size

The primary analysis will compare changes in PHQ9 scores at 6 months between intervention groups in all participants. We have powered the study, however, to be able to detect a between-group difference of 5.5 points on the PHQ9 score within the more severe subgroup of participants scoring 10 points or more on the PHQ9 at baseline. A difference of 5.5 points is used to reflect a category change on the PHQ9 and is clinically significant as well as statistically significant. Preliminary pilot RCT data, from a mixture of intervention and control group participants, showed that for those with a PHQ9 score of 10 or more at baseline, mean PHQ9 scores reduced from 17.7 to 10.8 points after the intervention, with a standard deviation of the changes of 6.1 points.

Based on a two-sample *t*-test, a sample size of 27 participants per arm would be required to have 90% power. In the pilot, follow-up data at the primary endpoint were available for approximately 65% of those randomized. To allow for this, 84 people (two groups of 42) with PHQ9 scores of 10 or more would need to be randomized. In the pilot, one-third of participants had PHQ9 scores less than 10 points at baseline, so that 126 participants in total (two groups of 63) will be randomized in this trial. We will ensure that the required number of participants scoring 10+ on the PHQ9 have entered the study before ending recruitment.

Our pilot study strongly supports our potential to recruit 126 participants using our multi-point recruitment strategy. We have not accounted for any clustering effects in these calculations, since clustering can only occur within the intervention group (control participants will not meet in a group setting during the first 6 months of the study), and the estimate of variation in the primary outcome used in the above calculation is conservative in that it includes a component due to clustering within intervention groups. As part of the analysis we will, however, assess the extent to which the study findings are sensitive to any clustering effects.

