#### Randomization

Randomization will be carried out at the Robertson Centre for Biostatistics at the University of Glasgow, part of the Glasgow Clinical Trials Unit, by staff not in direct contact with participants, and who will not carry out the final analysis. Randomization will occur each time sufficient participants have been recruited to fill two classes (up to 16 participants per class). Overall, we anticipate needing to run five immediate access (IA) classes and 5 DAC classes. Randomization will take into account timing of classes (availability to attend evening or daytime classes), location of classes (that is, classes in either Edinburgh or Glasgow), and severity of depression as measured by the PHQ9 (score of less than or equal to 9 and greater than or equal to 10) at the eligibility stage. Participants will be assigned to either IA or to DAC. Participants will then be given the date, time and place (IA or DAC) where their allocated classes will be held.

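### The SD is called conservative because it contains class variation, but that does not replace a design effect, and the primary ANCOVA as described has no class term

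*Protocol article*

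**What the plan says.** The section on statistical power and sample size (Protocol article) sizes the trial to "detect a between-group difference of 5.5 points on the PHQ9 score within the more severe subgroup", meaning participants with PHQ9 of 10 or more at baseline. It uses pilot data "from a mixture of intervention and control group participants", "with a standard deviation of the changes of 6.1 points", and concludes that "a sample size of 27 participants per arm would be required to have 90% power".

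On clustering it says: "We have not accounted for any clustering effects in these calculations, since clustering can only occur within the intervention group". It then adds a second reason, that "the estimate of variation in the primary outcome used in the above calculation is conservative in that it includes a component due to clustering" in the intervention groups. It does undertake to assess how sensitive the findings are to clustering.

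Under Randomization, "we anticipate needing to run five immediate access (IA) classes and 5 DAC classes". Under Statistical analyses, the primary analysis is a baseline-adjusted ANCOVA in all participants at 6 months, and no class effect is mentioned.

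**The concern.** Neither reason supports leaving clustering out.

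- **Clustering in one arm only.** This halves the penalty on the variance of the difference but does not remove it.
- **An SD that includes class variation.** That is the ordinary total SD, which is the input to a design effect and not a substitute for one. The between-class part of the IA mean averages over about five classes, not over 27 people, and the t-test formula treats it as if it averaged over people.

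The protocol's own wording presupposes a class component, so a positive ICC is its premise. The design makes one plausible: small interactive classes with group and pair tasks, each led by two presenters.

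Two things are at stake. The stated subgroup power would be lower than 90% on its own terms. More importantly, a primary model that treats classmates as independent gives a standard error that is too small whenever outcomes cluster.

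**Working it through.** **Inputs from the protocol.** Difference 5.5; SD of change 6.1; 27 evaluable per arm in the subgroup; 65% follow-up; 126 randomized (63 per arm); five IA classes.

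**Assumptions.** Two-sided alpha of 0.05 (not stated, but it reproduces the 27). ICC from 0.01 to 0.10 (none is given). Equal class sizes. Total SD of 6.1 in both arms, also applied to the all-participant analysis.

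**Step 1: the plan's own figures.**
- With 27 per arm, SE = √(2 × 6.1²/27) = 1.660, and 5.5/1.660 = 3.31. The noncentral t with 52 df gives power of 90.2%; 26 per arm gives 89.0%. So 27 reproduces.
- 27/0.65 rounds up to 42 per arm, or 84 in the subgroup, and 84/(2/3) = 126. Both reproduce, with no design effect anywhere.

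**Step 2: add the one-arm design effect in the subgroup.** m = 27/5 = 5.4, so DE = 1 + 4.4 × ICC. The variance of the difference is (6.1²/27) × (DE + 1), and the SE grows by √((1+DE)/2).

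| Assumed ICC | DE (IA) | SE | SE ratio | Power, ordinary df |
|---|---|---|---|---|
| 0 | 1.00 | 1.660 | 1.000 | 90.2% |
| 0.01 | 1.044 | 1.678 | 1.011 | 89.5% |
| 0.02 | 1.088 | 1.696 | 1.022 | 88.9% |
| 0.05 | 1.22 | 1.749 | 1.054 | 87.0% |
| 0.10 | 1.44 | 1.834 | 1.105 | 83.7% |

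**Step 3: all participants.** 63 × 0.65 ≈ 41 evaluable per arm, m = 41/5 = 8.2, DE = 1 + 7.2 × ICC.

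| Assumed ICC | DE (IA) | SE ratio | Power for 5.5, ordinary df |
|---|---|---|---|
| 0 | 1.00 | 1.000 | 98.1% |
| 0.01 | 1.072 | 1.018 | 97.7% |
| 0.05 | 1.36 | 1.086 | 96.0% |
| 0.10 | 1.72 | 1.166 | 93.3% |

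**Step 4: type I error of the plain ANCOVA.** I simulated 40,000 null trials per ICC, with 41 per arm, five IA classes, an assumed baseline–outcome correlation of 0.5, and the ICC placed on the baseline-adjusted residual. Two-sided rejection at nominal 5% was 5.0% at ICC 0, 5.5% at 0.01, 7.2% at 0.05 and 9.4% at 0.10. Simulations of an unadjusted t-test give nearly the same values (5.4%, 7.1% and 9.4% for the three positive ICCs). Baseline adjustment therefore does not remove the inflation.

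**Step 5: possible offsets to the power loss in the subgroup (ordinary df).**
- *Baseline adjustment.* The ratio of ANCOVA residual SD to change-score SD is √((1−r²)/(2(1−r))). It is 0.81 at r = 0.3 and 0.87 at r = 0.5 (both assumed). Power is then about 95% to 97% at ICC 0.05 and 92% to 95% at ICC 0.10.
- *Mixed-arm SD.* If the 6.1 was computed across both pilot arms and contained a 5.5-point arm difference, the within-arm SD would be √(6.1² − 5.5²/4) = 5.44. Power on the t-test basis is then about 93% and 91% at ICC 0.05 and 0.10.

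**The case against.** The strongest reply has four parts.

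1. **No ICC is documented, so no material loss is shown.** This stands. At ICC 0.01 to 0.02 the subgroup loses only about 1 point of power. A reader might infer that the trial is underpowered, but the protocol does not support that. The 90% is a t-test figure for a subgroup whose analysis is secondary, and the offsets in Step 5 could more than cover the loss. Those offsets are not, however, the reason the protocol gives for ignoring clustering.

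2. **The primary analysis has power to spare.** This also stands, on the assumption that SD 6.1 and 5.5 points carry over to all participants. But spare power does not correct a standard error that is too small.

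3. **Degrees of freedom for five classes would lower power further, so the loss is larger than Step 2 shows.** A reader might quote about 82% and 78% at ICC 0.05 and 0.10 in the subgroup. The same calculation gives 86.8% at ICC 0, so about 3 points of that drop are the price of the more cautious model and not an error in the stated 90%.

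4. **Clustering is disclosed and a sensitivity assessment is promised; its detail may sit in an analysis plan not shown.** This is fair, and the lack of model detail is not held against the article. It leaves two points that the article does fix: the reason it prints is wrong, and the analysis it names as primary is described without a class term.

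**Conclusion.** The concern holds in a limited form. The statement that the SD is conservative is a statistical error, and for any positive ICC both the subgroup power and the plain ANCOVA standard error err on the optimistic side. On the protocol's own t-test basis, power is about 89.5%, 87% and 84% at ICC 0.01, 0.05 and 0.10, given five equal IA classes and a total SD of 6.1. Net power below 90% is not established.

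The firmer consequence concerns the primary test. If outcomes cluster by class, its two-sided type I error is about 5.5%, 7% and 9% at those ICCs with 41 per arm, and its confidence interval is too narrow to match. It would go too far to say that the primary standard error will be too small, because that depends on an ICC which the protocol implies is positive but does not quantify.

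**What to change.** - Delete the sentence that calls the SD conservative.
- Restate subgroup power over ICC 0 to 0.10 with the one-arm design effect, labelling the ICCs as assumed. If the efficiency of baseline adjustment is relied on as an offset, say so and give the assumed correlation.
- Before analysis, pre-specify a partially nested ANCOVA as the primary model: random class effect in IA only, each delayed access participant as a singleton, and small-sample degrees of freedom (Kenward-Roger or Satterthwaite). Keep the plain ANCOVA as the sensitivity analysis.

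The cost is revised wording and one restated power figure. The confidence interval will be somewhat wider, and the class variance will be imprecisely estimated from about five classes. No extra participants are needed.

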#### Statistical analyses

The primary analysis will use analysis of covariance, testing the difference between groups in PHQ9 and GAD7 scores in all participants at 6 months with adjustment for baseline values. This is more efficient than two-sample *t*-tests, increasing the power of the study. An intention-to-treat approach to analysis will be used.

A criticism sometimes made of research studies that allow self-referral and utilize community-based recruitment is that patients are not significantly depressed. Planned secondary analyses will therefore be carried out for those with PHQ9 scores of 10 or more (that is, moderately severe depression), and for those with scores less than 10, at baseline. We will test whether the intervention effect interacts with baseline PHQ9 score (in other words, is the intervention more or less effective dependent upon the baseline PHQ9 score). The model for all participants will also be extended to assess the impact of baseline participant characteristics including age, gender, antidepressant use, level of depression and measures of compliance with the intervention (and, for those factors that influence outcome, their interaction with intervention). Similarly, regression methods, chosen according to the distribution of outcome variable being investigated, will be used for other outcomes. Simple and multiple imputation methods will be explored for the primary outcome to assess the sensitivity of the main study findings to alternative assumptions regarding missing data.

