## Abstract

**Background:**

Depression is a mental health condition which affects millions of people each year, with worldwide rates increasing. Cognitive behavioral therapy (CBT) is recommended in the National Institute for Health and Clinical Excellence (NICE) guidelines for the treatment of depression. However, waiting lists can cause delays for face-to-face therapy. Also a proportion of people decline to present for help through the health service – the so-called treatment gap. Self-referral to CBT using community-based group interventions delivered by a voluntary sector organization may serve to resolve this problem. The aim of this randomized controlled trial (RCT) is to determine the efficacy of such a guided CBT self-help course, the ‘Living Life to the Full’ (LLTTF) classes delivered by the charity Action on Depression (AOD). The primary outcome is level of depression at 6 months assessed using the patient health questionnaire-9 (PHQ9) depression scale. Secondary measures include levels of anxiety and social functioning.

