### Research questions

#### Primary question

Do the LLTTF classes result in an improvement in symptoms of depression and anxiety at 6 months compared to a DAC group, as measured by the patient health questionnaire-9 (PHQ9) [29] and generalized anxiety disorder 7 (GAD7) [30].

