### Patient health questionnaire-9

The primary outcome (PHQ9 depression scale) is at 6 months using an intention-to-treat analysis. PHQ9 is a freely available mood rating questionnaire consisting of nine questions mirroring DSM-IV depression diagnostic criteria [29]. The PHQ9 has shown diagnostic validity in a study of 3,000 adult patients. In this study, PHQ9 diagnosis rates were comparable with diagnosis by a mental health professional [29]. Each item is rated on a scale of 0 to 3, giving a maximum score of 27. Cut-off scores are used to label depression severity as: 0 to 4, minimal depression; 5 to 9, mild depression; 10 to 14, moderate depression; 15 to 19, moderately severe depression; 20 to 27, severe depression.

### Generalized anxiety disorder 7

The GAD7 is a seven-item questionnaire focusing on symptoms of anxiety experienced in the past 2 weeks [30]. Each item is rated according to the frequency of the described problem. The responses are scored as follows: 0 = ‘not at all’, 1 = ‘several days’, 2 = ‘more than half the days’, 3 = nearly every day’. Therefore the maximum score is 21. Studies of this measure have resulted in the authors stating the following cut of scores: 5 to 9, mild anxiety; 10 to 14, moderate anxiety; and 15 and above, severe anxiety. The GAD7 showed good reliability and criterion, construct, factorial, and procedural validity in a study carried out by the authors in 15 primary care clinics [30].

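### The protocol contradicts itself on whether the primary analysis is PHQ9 alone or PHQ9 and GAD7 together

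*Protocol article*

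**What the plan says.** Three places in the protocol article point to PHQ9 alone:

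- **Abstract, Background:** "The primary outcome is level of depression at 6 months assessed using the patient health questionnaire-9 (PHQ9) depression scale". The next sentence gives anxiety a lower rank: "Secondary measures include levels of anxiety and social functioning".
- **Measures, Patient health questionnaire-9:** "The primary outcome (PHQ9 depression scale) is at 6 months using an intention-to-treat analysis".
- **Statistical power and sample size:** "The primary analysis will compare changes in PHQ9 scores at 6 months between intervention groups in all participants".

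Two places put GAD7 beside PHQ9 at the primary level:

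- **Primary question (under Research questions):** the protocol asks "Do the LLTTF classes result in an improvement in symptoms of depression and anxiety at 6 months compared to a DAC group", with PHQ9 and GAD7 named as the measures.
- **Statistical analyses:** the primary analysis is an analysis of covariance "testing the difference between groups in PHQ9 and GAD7 scores in all participants at 6 months with adjustment for baseline values".

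The Statistical analyses section later plans imputation for the primary outcome in the singular. Under Secondary questions, GAD7 appears only within the two baseline PHQ9 strata (10 or more, and 5 to 9). GAD7 in all participants therefore has no place among the secondary questions.

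**The concern.** The sample size section and the Statistical analyses section follow one another, and each defines the primary analysis differently. If the two scales disagree, the verdict on the trial depends on which section is read. With PHQ9 null and GAD7 positive, the primary question and the Statistical analyses section would support a claim of success, while the Abstract, the PHQ9 paragraph and the sample size section would call the trial negative.

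An analysis plan written to this text cannot agree with all of it. If the choice were made after the results were known, the error rate of the primary claim would no longer be the nominal one.

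**Working it through.** **1. Which outcome the sample size supports.** Inputs from Statistical power and sample size: "to be able to detect a between-group difference of 5.5 points on the PHQ9 score within the more severe subgroup"; a pilot value "with a standard deviation of the changes of 6.1 points"; 90% power; a two-sample t-test; about 65% follow-up; one-third of participants below 10 on PHQ9. Neither alpha nor sidedness is stated, so I assume two-sided 5%.

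- Normal approximation: n = 2(1.96 + 1.2816)² × 6.1² / 5.5² = 25.9, so 26 per arm.
- Exact t-test: 27 per arm, power 90.2%. This is the stated figure. A one-sided 5% test would need only 22 (normal approximation), so two-sided 5% is the reading that fits.
- Loss to follow-up: 27 / 0.65 = 41.5, so 42 per arm and 84 in total. This matches the protocol.
- Adding the milder third: 84 / (2/3) = 126. This matches the protocol.

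The calculation is reproduced in full and uses PHQ9 only. The document gives no GAD7 difference or standard deviation.

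**2. Error rate if either scale sufficed.** Assume each scale is tested at two-sided 5%. Let Z1 and Z2 be the two test statistics under no effect, bivariate normal with correlation r. The document does not give r, so a range is shown.

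- At least one false positive in either direction: 1 − P(|Z1| < 1.96 and |Z2| < 1.96). At r = 0 this is 1 − 0.95² = 0.0975.
- At least one false claim of benefit: 1 − P(Z1 < 1.96 and Z2 < 1.96). At r = 0 this is 1 − 0.975² = 0.0494, against a nominal 2.5%.

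| Assumed r | Either direction | Benefit only |
|---|---|---|
| 0 | 9.75% | 4.94% |
| 0.5 | 9.07% | 4.54% |
| 0.6 | 8.75% | 4.38% |
| 0.7 | 8.35% | 4.17% |
| 0.8 | 7.81% | 3.90% |

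**3. Error rate if both scales were required.** A false claim then needs two false positives at once, so the rate cannot exceed 5%. There is no inflation.

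**4. The two ways to resolve it.**

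- PHQ9 as sole primary outcome: alpha stays at 5%, and the sample size stays at 27 evaluable per arm in the more severe subgroup and 126 randomized.
- Both scales as primary, with alpha split equally (two-sided 2.5% each): for PHQ9, 32 per arm by the t-test; 32 / 0.65 = 49.2, so 50 per arm and 100 in total; 100 × 1.5 = 150 randomized. With 27 per arm kept, PHQ9 power falls from 90.2% to 83.9%. GAD7 power still could not be calculated.

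**The case against.** The best defence is that this is loose wording rather than two primary outcomes. Nowhere is GAD7 called a primary outcome: where that term is tied to a scale, the scale is PHQ9, and the section that adds GAD7 to the primary analysis later returns to the singular. That makes PHQ9 the likely intention. It does not remove the conflict, because the primary question and the primary analysis are what readers and analysts work from, and both include GAD7.

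A reader might also draw four stronger conclusions that the document does not support:

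- **That the trial has two chances to succeed.** No section says either scale is enough, so the inflation above is conditional on that reading and on the assumed 5% level.
- **That a multiplicity rule is missing.** Testing order and alpha allocation are commonly left to an analysis plan, and none is shown here. Their absence cannot be held against this article. Which outcome is primary can be, because the article states it in two incompatible ways.
- **That requiring both scales would take power below 90%.** The 90% belongs to a t-test in participants with baseline PHQ9 of 10 or more, whereas the disputed analysis is a covariance analysis in everyone. With 63 × 0.65 ≈ 41 per arm, and if the same 5.5 points and SD of 6.1 applied to all, t-test power for PHQ9 alone would be about 98%. A smaller effect in milder participants would lower it. With no GAD7 inputs, joint power cannot be judged either way.
- **That several sections rank anxiety as secondary.** Only the Abstract does; the PHQ9 paragraph and the sample size section are silent on it.

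**Conclusion.** The contradiction stands and is in the current text: three places make PHQ9 the sole primary outcome or analysis, and two add GAD7. Its consequence is that one pattern of results, null PHQ9 with positive GAD7, can be reported as a success or as a failure.

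The numerical cost depends on a rule the document does not give. Under an either-scale reading, with two-sided 5% per scale and correlations from 0.8 down to 0 (all assumed), the false-positive chance is 7.8% to 9.75%, or 3.9% to 4.9% for claims of benefit. Under a both-scales reading there is no inflation. The sample size is not wrong, but it supports PHQ9 only. The point should be settled before the groups are compared.

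**What to change.** In Primary question and in Statistical analyses, name PHQ9 at 6 months in all participants as the sole primary outcome. Add GAD7 in all participants to Secondary questions, either tested only after PHQ9 succeeds or reported without a confirmatory claim; both options are acceptable. This follows the position already taken in the Abstract, the PHQ9 paragraph and the sample size section.

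The cost is a few lines of wording. The total of 126, the design and the data collection are unchanged. The one loss is GAD7's primary status, which the sample size never supported. Trial status reports 104 participants already randomized, so the change should be dated and made before any between-group analysis. Whether the registry entry needs the same correction cannot be told from this document and should be checked.

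### The primary ANCOVA is stated with baseline adjustment, and class timing and city, which randomization takes into account, are named in no model; the effect is mildly conservative

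*Protocol article*

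**What the plan says.** On allocation, the Randomization section reads: "Randomization will take into account timing of classes (availability to attend evening or daytime classes), location of classes". The locations are the two cities, Edinburgh and Glasgow. The third factor is PHQ9 severity when eligibility is assessed, split into 9 or below against 10 or above. Randomization takes place each time enough people have been recruited to fill two classes, and five immediate-access and five delayed-access classes are anticipated.

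On analysis, the Statistical analyses section reads: "The primary analysis will use analysis of covariance, testing the difference between groups in PHQ9 and GAD7 scores in all participants at 6 months", and continues "with adjustment for baseline values". It justifies ANCOVA as more efficient than two-sample t-tests. A later, extended model looks at "baseline participant characteristics including age, gender, antidepressant use, level of depression and measures of compliance with the intervention". The sample size section adds a sensitivity assessment for clustering. That concerns people taught in the same class, not the allocation factors.

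**The concern.** When allocation is balanced on a factor, the factor contributes less to the chance difference between arms than it would under simple randomization. A model that leaves the factor out still counts its full variance as residual error. The reported standard error then overstates the true variability of the treatment estimate, and the test rejects less often than its nominal level. The usual remedy is to put the balancing factors in the model.

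Here two of the three factors, timing and city, appear in no stated model. The third, severity, is largely covered in the PHQ9 model by the continuous baseline PHQ9. It is not covered in a GAD7 model adjusted only for baseline GAD7, and GAD7 is part of the stated primary analysis.

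What is at stake is some precision and a confidence interval slightly wider than it need be. Availability in the daytime may go with work status, so an association between timing and outcome is plausible, but the article gives no evidence either way.

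**Working it through.** **The plan's own figure.** Inputs from the sample size section: difference 5.5 points, SD of change 6.1, 90% power, two-sample t-test. The article states no alpha; 0.05 two-sided is assumed.
- Exact t-test power is 89.0% with 26 per arm and 90.2% with 27 per arm, so 27 per arm reproduces.
- Loss to follow-up: 27 / 0.65 = 41.5, so 42 per arm and 84 in all.
- One-third expected below 10 points: 84 / (2/3) = 126.
- Expected completers: 126 × 0.65 = 81.9, about 82.

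The sample size is therefore correct. It rests on an unadjusted t-test, so this point does not change it.

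**What omitting the factors does.** Let R be the share of residual variance (after the baseline score) that timing and city explain. The article gives no value, so R is assumed. The reported variance of the treatment estimate is proportional to 1.

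*If balance held exactly among those analysed*, the true variance would be proportional to 1 − R. The reported standard error would be too large by the factor 1/√(1 − R), and the size would be 2 × [1 − Φ(1.96/√(1 − R))].

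*In this trial* balance applies to those randomized, while about 65% are expected to be followed up. If loss is random, 35% of the factors' contribution to chance imbalance returns among completers. The true variance is then proportional to (1 − R) + 0.35R = 1 − 0.65R.

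| Assumed R | 1 − 0.65R | Standard error too large by | Two-sided size | Same under exact balance |
|---|---|---|---|---|
| 0% | 1 | 0% | 5.0% | 0%; 5.0% |
| 5% | 0.9675 | 1/√0.9675 = 1.017, so 1.7% | 2 × [1 − Φ(1.993)] = 4.6% | 2.6%; 4.4% |
| 10% | 0.935 | 1/√0.935 = 1.034, so 3.4% | 2 × [1 − Φ(2.027)] = 4.3% | 5.4%; 3.9% |

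A simulation with 35% random loss gave sizes of 4.7% and 4.4% at R = 5% and 10%, in line with the table.

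**What adding the factors gains.** A simulation used 80 completers, residual SD 6.1 (assumed), an illustrative 4-point difference and exact balance within the four timing-by-city cells. Power without and with the factors was 82.6% and 83.8% at R = 5%, and 83.3% and 85.9% at R = 10%. At R = 0 there was no difference (81.6% both ways).

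**Degrees of freedom.** With 82 completers, intercept, arm and baseline score leave 79. Timing and city take 2, leaving 77. PHQ9 severity in the GAD7 model takes one more, leaving 76.

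**The case against.** The strongest reply is that the article does not say baseline values are the sole covariates. The extended-model list is open-ended, the article condenses a fuller plan, and an analysis plan that is not shown may include timing and city. That is fair, and nobody should infer that the plan rules these factors out. But the article does state the adjustment in its primary model and names covariates for a further model, and timing and city are in neither. Naming them is a concrete change to a stated method, not a request for detail that an article would normally leave out.

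Second, the article says only that randomization takes the factors into account; it does not say stratified or minimized. A reader might take exact balance within strata as given, but the text does not establish it. The argument applies under either method. If timing and location served mainly to place people in classes they could attend, with little balancing, the effect would be smaller still.

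Third, a reader might apply the exact-balance figures (sizes of 4.4% and 3.9%). They do not fit this trial, because the plan expects to lose about 35% of those randomized and balance does not carry over intact to completers. This objection stands, and the smaller figures are the ones to use.

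Fourth, the sample size never relied on this precision: it was set to "detect a between-group difference of 5.5 points on the PHQ9 score within the more severe subgroup" by an unadjusted t-test. This also stands. It would be too strong to say that the precision bought by the allocation scheme is lost.

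**Conclusion.** The point holds as a modest improvement to the stated primary model. Timing and city are taken into account at allocation and appear in no stated analysis, and the GAD7 model as stated also leaves out PHQ9 severity. The consequence is conservative: no bias, and a false-positive rate at or slightly below 5%. A reader might infer that the test is invalid or the result untrustworthy; the documents do not support that.

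The size rests on three assumptions: that the allocation method does balance the factors, that loss to follow-up is about 35% and random, and that the factors explain 5% to 10% of residual variance. The direction is certain if the factors are balanced and prognostic. The amount is not, and it could be nil.

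**What to change.** Before outcome data are analysed, state the primary model as: 6-month score = arm + baseline score + class timing (evening or daytime) + city. For GAD7, add PHQ9 severity, either as the eligibility-stage stratum or as continuous baseline PHQ9. For PHQ9, the continuous baseline score largely serves that purpose already.

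Do not require a term for recruitment batch. With about five pairs of classes it would take about 4 degrees of freedom. If each pair shares a city and a time slot, batch would determine both and the terms could not be separated.

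The cost is a line of analysis wording and 2 degrees of freedom for PHQ9 or 3 for GAD7, out of about 80. The factors are used at allocation, so they should be on record for everyone randomized. The Trial status section reports 104 people already randomized, so the change should be dated and made before results are seen; covariates added afterwards would be open to challenge.
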